### Recruitment of Patients

Patients will be recruited from the ROADMAP tapering clinic at the Freeman Hospital in Newcastle Upon Tyne, UK. Patients are referred to this National Health Service (NHS) by their usual rheumatology clinician, having identified that they have a clinical diagnosis of RA that is in remission and the patient is willing to consider DMARD tapering.

Prior to their first ROADMAP clinic visit, patients will be posted the study participation information sheet to read beforehand (Figure 1). After completion of their first ROADMAP clinic visit, patients will be able to discuss the study further with a study investigator who can answer any questions they have about the study. Patients who would like to participate can then immediately enroll for their baseline study visit (ie, at the same hospital attendance as their ROADMAP appointment). Subsequent study visits are then scheduled to coincide with ROADMAP appointments to avoid additional clinic visits.

**Figure 1. F1:**
[figure not shown]
Overview of the study protocol, showing the planned study flow and key procedures across study phases. CRP: C-reactive protein; HAQ-DI: Health Assessment Questionnaire Disability Index; NHS: National Health Service; RA-FQ: Rheumatoid Arthritis Flare Questionnaire; ROADMAP: Rheumatoid Arthritis DMARD Tapering; VAS: visual analog scale.

### Study Visits

#### Baseline Visit

Following the completion of the ROADMAP, patients attend baseline study visit (day 0). Patients attending their initial appointment will first undergo the inclusion and exclusion criteria check (Textbox 2).

Once the inclusion and exclusion criteria check is complete, patients will undergo the following study procedures in sequence. First, all patients will have the opportunity to discuss the study further with a study investigator before signing the consent form. Patients will next provide baseline information, including age, sex, address, telephone number, email address, past medical history, Clinical Frailty Score, Charlson Comorbidity Index, current medications, smoking status, and alcohol intake, after which height and weight will be recorded [16,17]. For each DMARD, the drug name and class, route, current dose and dosing frequency, reference therapeutic dose, proportion of the reference dose at enrollment, date and magnitude of the most recent dose reduction, number of previous tapering steps, and planned next tapering step will also be recorded. A researcher will then examine the patient to document the 28-joint tender and swollen counts, patient visual analog scale, and physician visual analog scale required for 28-joint Disease Activity Score with C-reactive protein (DAS28-CRP) disease activity assessment, and CRP blood test results obtained as part of routine clinical care during the ROADMAP clinic visit will also be recorded for DAS28-CRP calculation (Multimedia Appendix 2) [5,18].

Textbox 2.Inclusion and exclusion criteria for study participation.
**Inclusion criteria**
Clinical diagnosis of rheumatoid arthritis (RA) made by a consultant rheumatologist28-joint Disease Activity Score with C-reactive protein (DAS28-CRP)<2.4 at point of enrollment to the studyCurrent (or expected within the next 28 days) tapering of a disease-modifying antirheumatic drug (DMARD; conventional synthetic, targeted synthetic, or biologic)Able to walk at least 4 m independently without walking aidsPatient willing to commit to complete remote Rheumatoid Arthritis Flare Questionnaire (RA-FQ) and continuously wear monitoring devices
**Exclusion criteria**
Current or recent (within past 12 months) use of rituximabCurrent or recent (within past 12 months) use of oral, intramuscular, intravenous, or intra-articular glucocorticoids for arthritis treatment (note that topical glucocorticoids and short courses of systemic glucocorticoids for other indications such as lung or skin conditions are permitted)Escalation of DMARD therapy (ie, initiation of new DMARD or increase in DMARD dose) within past 12 months (note that dose reductions are permitted)Unable to read or communicate in EnglishInability to provide informed consentAge less than 18 yearsCurrent diagnosis of a movement disorderPhysical disability that would prevent wearing a wrist device (eg, bilateral upper limb amputation or congenital deformity)Current pregnancy

Patients will then complete the Health Assessment Questionnaire Disability Index (HAQ-DI) and the RA-FQ paper questionnaire [19]. They will subsequently be shown how to access the REDCap online portal to complete weekly online RA-FQ; if a patient cannot access the online platform because of limited internet or device access or limited digital literacy, they will be provided with a pack of 12 paper RA-FQs to complete weekly [11]. Patients will also be instructed, with written guidance, on how to wear the Axivity AX6 devices (Figure 2). Three Axivity AX6 devices and 1 wrist strap will be provided, and patients will wear each device on the nondominant wrist, or the dominant wrist if needed, in sequence for 28 days each, providing a continuous 3-month recording period. Finally, the study researcher will record whether the patient satisfies the ACR/EULAR 2010 RA Classification Criteria based on a retrospective review of clinical notes (Multimedia Appendix 3) [2].

**Figure 2. F2:**
[figure not shown]
Participants will wear the device with the arrow on the device aligned with the arrow on the inside surface of the strap. The device was positioned so that the electrical pulse signal on the outside of the rubber strap faced the thumb, regardless of whether it was worn on the right or left wrist.

#### Month 3 Visit (±1 Week)

At the week 12 visit, within a 1-week window, patients will be asked to verbally confirm their willingness to continue in the study, and any changes in concurrent medications and any adverse events (AEs) since the last clinic visit will be recorded. A researcher will then assess the 28-joint tender and swollen counts, patient visual analog scale, and physician visual analog scale required for DAS28-CRP disease activity assessment. The patient will complete an HAQ-DI questionnaire and an RA-FQ paper questionnaire, unless an online RA-FQ has already been completed within the previous 24 hours. Any paper questionnaires provided at the last visit and the Axivity AX6 devices from the previous study visit will be collected. If arthritis flare is confirmed, defined as a DAS28-CRP of at least 2.4 or at least 1 swollen joint, this will already have been treated appropriately during the concurrent ROADMAP clinic appointment, and the study investigator will record the patient’s estimated date of flare onset.

All patients will then be offered enrollment in the optional 12-week extension study. If the patient agrees, they will immediately enter the extension phase, be provided with 3 new Axivity AX6 devices and 1 wrist strap to wear for 28 days each in sequence on the nondominant wrist, or the dominant wrist if needed, and, if they are unable to access the online REDCap portal, they will also be given 12 additional paper RA-FQs to complete weekly; their next and final study visit will take place 12 weeks later, 84 days, according to schedule 6.3. If the patient declines the optional extension, they will exit the study at this visit and will be given a feedback questionnaire on the usability and acceptability of the AX6 devices together with a stamped addressed envelope for postal return to the study team.

#### Extension Study: Months 6, 9, and 12 Visits (±1 Week)—If Participating in Optional Extension Study

Participants entering the optional extension may attend follow-up visits at month 6 (week 24 ±1 wk), month 9 (week 36 ±1 wk), and month 12 (week 52 ±1 wk). At the month 6 and month 9 visits, participants will verbally confirm their willingness to continue. Changes in concurrent medications and any AEs since the previous visit will be recorded at each visit. A researcher will assess the 28-joint tender and swollen joint counts and the patient and physician visual analog scales. CRP results obtained through routine clinical care will also be recorded to calculate the DAS28-CRP. Participants will complete the HAQ-DI and a paper RA-FQ unless they have completed the online RA-FQ within the preceding 24 hours.

A clinically confirmed flare will be defined as a DAS28-CRP of ≥2.4 and/or at least 1 swollen joint attributable to inflammatory RA activity. Confirmed flares will be managed by the ROADMAP clinical team as part of routine care, and the study investigator will record the estimated date of flare onset. At each visit, completed paper questionnaires and Axivity AX6 devices from the preceding monitoring period will be collected. Participants who do not wish to continue at month 6 or month 9 will complete the wearable usability and acceptability questionnaire and exit the study. All participants remaining in the study at month 12 will complete the questionnaire and exit the study. No participant will be followed for more than 12 months from baseline. These optional extension visits will be implemented only after approval of the submitted ethics amendment and all required sponsor and site approvals.

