## Methods

### Study Design

This prospective, single-center observational cohort study is embedded within the ROADMAP DMARD tapering clinic at Freeman Hospital, Newcastle upon Tyne, United Kingdom (Multimedia Appendix 1). Adults with clinician-confirmed RA in remission who are undergoing or are about to begin DMARD tapering will be followed for 9 months. Continuous wrist-worn accelerometry and weekly RA-FQ responses will be collected throughout follow-up, with clinical assessments aligned with routine ROADMAP visits at baseline and approximately months 3, 6, 9, and 12 together with ad hoc visits for suspected flare.

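### The 84-day device and paper-form kit has not been reconciled with an extension schedule whose last interval is 112 days, and it has no slack for the ±1 week visit windows

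*Protocol article*

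**What the plan says.** **Supply.** The baseline procedures (in the text that follows the exclusion criteria) state that "Three Axivity AX6 devices and 1 wrist strap will be provided", to be worn "in sequence for 28 days each, providing a continuous 3-month recording period". Participants without usable online access get paper forms: "they will be provided with a pack of 12 paper RA-FQs to complete weekly". At the Month 3 Visit, a participant who enters the extension will "be provided with 3 new Axivity AX6 devices and 1 wrist strap to wear for 28 days each in sequence", with 12 more paper forms if needed. The Ad Hoc Flare Visits section gives the same kit to a participant who enters the extension after a confirmed flare.

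**Interval.** The Month 3 Visit section ties that kit to one further visit: "their next and final study visit will take place 12 weeks later, 84 days, according to schedule 6.3". The Ad Hoc Flare Visits section likewise treats the extension as a single 12-week period.

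**Schedule.** The section on the extension visits instead lists "month 6 (week 24 ±1 wk), month 9 (week 36 ±1 wk), and month 12 (week 52 ±1 wk"). On equipment it says only: "At each visit, completed paper questionnaires and Axivity AX6 devices from the preceding monitoring period will be collected". It gives no number of devices or forms issued at month 6 or month 9. It also caps follow-up at 12 months from baseline.

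**Intended data and analysis.** Study Design states: "Continuous wrist-worn accelerometry and weekly RA-FQ responses will be collected throughout follow-up". Primary Analyses sets weekly landmarks, each predicting flare over the next 14 days. Missing Data fills absent accelerometry by last observation carried forward (LOCF).

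**The concern.** Weeks 0 to 12, 12 to 24 and 24 to 36 are each 12 weeks and match the kit exactly. Weeks 36 to 52 are not 12 weeks. The supply and period wording appears to have stayed with a single 12-week extension while the visit schedule was lengthened.

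What is at stake is the end of follow-up, where a scheduled clinical assessment can establish the primary outcome. If devices run out before that visit, the weekly predictions continue to be computed, but from values carried forward because nothing new was recorded. LOCF is justified in the plan as reflecting the information available at the time of prediction. That reasoning suits an occasional missed day better than a block of weeks with no device to wear. Accuracy at those landmarks would say little about what live monitoring can do.

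**Working it through.** **Inputs.** Three devices, 28 days each, and 12 weekly forms (baseline, Month 3 Visit, Ad Hoc Flare Visits). Visits at weeks 12, 24, 36 and 52, each ±1 week, with baseline at day 0. Horizon 14 days, weekly landmarks (Primary Analyses).

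**Step 1: the plan's own figure.** Devices: 3 × 28 = 84 days. Paper forms: 12 × 7 = 84 days. Interval given at month 3: 12 × 7 = 84 days. These agree.

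**Step 2: gap per interval.** Interval = (later week − earlier week) × 7, with each visit moved within its window. Gap = interval − 84. A negative gap means spare capacity.

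| Weeks | Nominal (gap) | Shortest (gap) | Longest (gap) | Kit stated? |
|---|---|---|---|---|
| 0–12 | 84 (0) | 77 (−7) | 91 (7) | yes |
| 12–24 | 84 (0) | 70 (−14) | 98 (14) | yes |
| 24–36 | 84 (0) | 70 (−14) | 98 (14) | no |
| 36–52 | 112 (28) | 98 (14) | 126 (42) | no |

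For the last row the shortest case is week 37 to week 51, (51 − 37) × 7 = 98, and the longest is week 35 to week 53, (53 − 35) × 7 = 126. If the 12-month cap ends follow-up at week 52, the longest becomes (52 − 35) × 7 = 119, a gap of 119 − 84 = 35 days. Rows marked "no" assume that the described kit is reused.

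**Step 3: what this does to the landmarks, nominal case.** Devices issued at week 36 run out at week 36 + 12 = 48. The week-48 landmark has current data, and its 14-day horizon ends at week 50. Landmarks at weeks 49, 50, 51 and 52 rest on carried-forward values. A flare dated to the week-52 visit lies within 14 days of the landmarks at weeks 50 and 51 only, where the last recorded day is (50 − 48) × 7 = 14 and (51 − 48) × 7 = 21 days old. No landmark with current data reaches it.

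**Step 4: best case.** Devices issued at week 37 run out at week 49. The week-49 landmark still has current data, and its horizon ends at week 51, the date of the visit. A 14-day gap therefore does not remove the 14-day-ahead prediction. It removes only the later updates.

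**Step 5: supply needed.** Nominal last interval: 112 / 28 = 4 devices and 112 / 7 = 16 forms. Longest in-window interval: 126 / 28 = 4.5, so 5 devices, and 126 / 7 = 18 forms. Earlier intervals at their longest: 98 / 28 = 3.5, so 4 devices, and 98 / 7 = 14 forms (91 / 7 = 13 before month 3).

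**The case against.** The strongest reply is that nothing says what is handed out at month 9. The 84-day kit is stated for baseline, for entry to the extension at month 3 and for entry after an ad hoc flare visit. Issuing four devices at month 9 would contradict no sentence in the article, and device counts per visit are the kind of detail an article leaves to the full protocol. This stands. A reader might infer that there will be no accelerometry before every month-12 visit. The document does not support that, and the 28-day figure holds only if the described kit is reused.

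Four further limits also stand:

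- Landmark predictors come from data before the landmark, so a gap as long as the horizon is not in itself fatal (Step 4). Carried-forward values are one day old at the start of a gap and become stale only as it lengthens.
- The investigator records an estimated onset date, which may fall before the devices stop, and ad hoc visits can catch symptomatic flares earlier. How many first flares would be affected cannot be derived from the document.
- The RA-FQ shortfall concerns paper users only. Online completion is not limited to 12 forms.
- Month 9 and month 12 visits depend on an ethics amendment still under review.

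The reply does not dispose of two things. The month 3 and ad hoc sections describe one 12-week extension, with a final visit at its end, while the extension section lists three visits up to week 52. That is a conflict in the text, not an omitted detail. A participant who flares after week 36 is told to wear the devices for the rest of a 12-week extension period that the schedule does not contain. And the two kits that are stated explicitly leave nothing for a late visit.

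**Conclusion.** The point holds as a failure to reconcile supply with schedule. Without any inference about month 9, the stated kits leave up to 7 unrecorded days before month 3 and up to 14 between months 3 and 6 when visits fall at the edges of their windows, and the extension is described in two incompatible ways. If the same kit is reused at month 9, the gap before the month-12 visit is 28 days nominally, 14 at best, and about 35 at most under the 12-month cap (42 if week 53 is allowed). In the nominal case about the last four weekly landmarks would run on carried-forward data, and a flare dated to week 52 would lie beyond the horizon of every landmark with current data. Flares with an earlier estimated onset, or found at ad hoc visits, are less affected.

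These figures assume that each device yields data for its stated 28 days and no longer, that wear starts on the day of issue, and that landmarks fall on whole weeks from enrollment.

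The gap is still preventable. The first participant enrolled on October 9, 2025, so by July 1, 2026 (265 days, about week 38) nobody could have reached week 48, and approved follow-up is 6 months.

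**What to change.** 1. Reconcile the 12-week extension wording in the Month 3 Visit and Ad Hoc Flare Visits sections with the schedule for months 6, 9 and 12, including what a participant who flares late in the extension does with the devices.
2. Either align the visit weeks with the 84-day kit, or state the supply at each extension visit, with at least 4 devices and 16 paper forms at month 9.
3. Under either option, issue one spare device and 1 to 2 spare forms at every visit to cover the ±1 week windows.
4. In the analysis, do not score a landmark as current once the participant's devices have run out. Report such landmarks separately or exclude them, and do not let LOCF bridge the gap unmarked.

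The cost is one or two extra devices and a few forms per participant. If settled before the extension starts, the change adds no visits.

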#### Ad Hoc Flare Visits (Throughout the Study)

Patients tapering their DMARDs in the ROADMAP clinic may request additional ad hoc visits outside the usual 3-monthly schedules if they suspect an arthritis flare. There is no limit to the number of ad hoc visits, although in practice only one ad hoc visit would usually be expected for a patient who experiences a flare. In these cases, the patient will contact the study team to report possible flare symptoms, and a study investigator will then contact the ROADMAP clinic administrative team to arrange a ROADMAP clinic appointment and book a study visit to coincide with it. At the start of the ad hoc visit, patients will be asked to verbally confirm their willingness to continue in the study. Any changes in concurrent medications and any AEs since the last clinic visit will be recorded. A researcher will then assess the 28 joint tender and swollen counts, patient visual analog scale, and physician visual analog scale required for DAS28-CRP disease activity assessment. CRP blood test results obtained during routine clinical care at the ROADMAP clinic visit will also be recorded for DAS28-CRP calculation. The patient will then complete an HAQ-DI questionnaire and an RA-FQ paper questionnaire, unless an online RA-FQ has already been completed within the previous 24 hours.

If arthritis flare is confirmed, defined as a DAS28-CRP of at least 2.4 or at least 1 swollen joint, this will already have been treated appropriately during the concurrent ROADMAP clinic appointment. The study investigator will record the estimated date of flare onset, and follow-up in the main study period will be terminated if not already completed. Patients who are not already enrolled in the optional 12-week extension study will be offered enrollment. If they agree, they will immediately enter the extension phase, any paper questionnaires and Axivity AX6 devices from the last visit will be collected, and they will be provided with 3 new Axivity AX6 devices and 1 wrist strap to wear for 28 days each in sequence on the nondominant wrist, or the dominant wrist if needed. If they cannot access the online REDCap portal, they will also be given 12 additional paper RA-FQs to complete weekly, and their next study visit will take place in 12 weeks according to schedule 6.3, replacing the planned week 12 main study visit. If the patient is already enrolled in the optional extension study, they will be given a feedback questionnaire on AX6 usability and acceptability, will continue wearing the AX6 monitors and completing any provided paper RA-FQs for the remainder of the ongoing 12-week extension period, and will then exit the study without an extension week 12 review to avoid an extra visit outside the ROADMAP clinic schedule; they will also be given a stamped addressed envelope to return the AX6 monitors and paper questionnaires by post. If a patient with confirmed flare declines the optional extension study, they will exit the study at that visit, any paper questionnaires and AX6 devices from the last visit will be collected, and they will be given a feedback questionnaire on AX6 usability and acceptability together with a stamped addressed envelope for postal return to the study team. If arthritis flare is not confirmed, the patient will continue to wear the Axivity AX6 monitors and complete RA-FQs according to the current schedule and will attend the next study visit as already arranged.

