##### RA-FQ

The RA-FQ is also designed to remotely monitor patients with RA during drug tapering. Participants rate, on a 0‐10 scale, their pain, difficulty with physical activities, fatigue, joint stiffness, and challenges in daily activities such as work, over the past week. At the end of the questionnaire, 2 yes or no questions ask whether the patient has experienced these symptoms for more than 1 week and whether they believe they are currently experiencing a flare of RA. The responses provide a standardized way to assess symptom severity and detect flares, helping clinicians track disease activity and adjust treatment if needed. The questionnaire will be collected weekly for each patient. For the 0‐10 scale items, the average score for each symptom will be calculated across all patients at 4 main visit time points, and summary statistics (eg, mean, SD, and/or median, IQR, and range) will be reported.

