The model will be generated at weekly landmark times throughout follow-up. At each landmark, the model will use all accelerometry data collected up to that time to estimate the probability of clinician-defined flare occurring within the subsequent 14 days. Weekly updating allows risk estimates to be refreshed throughout DMARD tapering and provides clinically actionable information to support decisions regarding continuation or modification of tapering.

We will also evaluate the accuracy of the model’s flare predictions for each prediction time window against patient-reported flares derived from the RA-FQ, based on responses to the yes or no question about current flare status. Patient-reported flare status will serve as the reference standard. Model-predicted flares will be compared against patient reports to calculate sensitivity, specificity, and agreement (Cohen κ). It helps to assess how well the model’s predictions align with patient perception.

Sensitivity: proportion of patient-reported flares that are correctly predicted by the model (true-positive rate); higher values, close to 100%, are desirable.Specificity: proportion of patient-reported nonflares that are correctly identified as no flare by the model (true-negative rate); higher values, close to 100%, are desirable.Agreement: measured using Cohen κ to quantify concordance between model-predicted and patient-reported flares; higher values, close to 1, indicate stronger agreement beyond chance.

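### At month 3 and ad hoc visits the patient VAS and visit-day RA-FQ may be answered after the clinical flare verdict, which risks inflating agreement between patient-reported and clinically confirmed flare

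*Protocol article*

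**What the plan says.** All references are to the protocol article.

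- **Month 3 Visit.** The researcher takes joint counts and the patient and physician VAS. Then: "The patient will complete an HAQ-DI questionnaire and an RA-FQ paper questionnaire, unless an online RA-FQ has already been completed" in the previous 24 hours. A confirmed flare is described in these terms: "this will already have been treated appropriately during the concurrent ROADMAP clinic appointment".
- **Ad Hoc Flare Visits.** The study team arranges a ROADMAP appointment and is to "book a study visit to coincide with it". Joint counts and VAS come first, and next "The patient will then complete an HAQ-DI questionnaire and an RA-FQ paper questionnaire", with the same 24-hour online exception. The statement that a flare has already been treated is repeated.
- **Extension Study (months 6, 9 and 12).** The same measures are taken, but the text says only this about timing: "Confirmed flares will be managed by the ROADMAP clinical team as part of routine care". It does not say whether the consultation precedes the study assessment.
- **RA-FQ.** The form is completed weekly. One of its two closing yes/no items asks patients "whether they believe they are currently experiencing a flare of RA".
- **Primary Analyses.** For the comparison of model predictions with patient-reported flare: "Patient-reported flare status will serve as the reference standard".
- **Primary and secondary objectives (Textbox 1).** RA-FQ accuracy against clinically confirmed flare is a secondary subobjective.
- **Introduction.** A patient-rated VAS is one of the four ingredients of DAS28.

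Nowhere does the article place the VAS or RA-FQ before the consultation, or provide for marking forms completed after it.

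**The concern.** The RA-FQ flare item asks for a belief. Someone who has just been told by a clinician that the arthritis is, or is not, flaring may answer in line with that verdict. Two of the planned comparisons use this item: the model against patient-reported flare (a primary subobjective) and RA-FQ against clinically confirmed flare (a secondary one). If some answers follow the verdict, the two flare definitions are no longer independent at the moments when they are compared most directly.

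The drift would favor agreement in both directions. After a verdict of flare, a would-be no can become a yes, which raises apparent sensitivity. After a verdict of no flare, a would-be yes can become a no, which raises apparent specificity. Either way, the result says less about what a questionnaire answered at home would detect, and remote detection is the study's question.

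**Working it through.** The article gives no figure to reproduce here. The check is a reading of the stated order, followed by simple ratios for how much data could be touched.

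**Step 1: order of events, visit by visit.**
- *Baseline:* the study visit follows the ROADMAP visit (Recruitment of Patients; Baseline Visit). Consent is given after the consultation, so this order is unavoidable there.
- *Month 3 and ad hoc:* the flare has already been treated when the study visit confirms it. The words concurrent and coincide are loose, but already implies that the verdict came first.
- *Months 6, 9 and 12:* not stated.

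**Step 2: order within the study visit.** At ad hoc visits the RA-FQ is placed explicitly after the joint counts and VAS. At month 3 it is listed in that order. The RA-FQ can therefore also follow the researcher's joint examination.

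**Step 3: who avoids it.** Participants with an online RA-FQ in the previous 24 hours need no visit-day form. The exception covers online forms only, so a paper user always completes the visit-day form. No exception applies to the patient VAS.

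**Step 4: share of all RA-FQs.** With weekly forms and one scheduled visit about every 12 to 13 weeks:
- one 12- to 13-week period: 1/13 = 7.7% to 1/12 = 8.3%;
- 12 months with four follow-up visits: 4/52 = 7.7%;
- the same with one ad hoc visit added: 5/53 = 9.4%.

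These are upper limits, because the 24-hour exception lowers them. About 90% or more of RA-FQs are completed away from visits.

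**Step 5: share of the records nearest to a confirmed flare.** Clinical confirmation happens only at a visit. Each confirmed flare therefore comes with either a visit-day RA-FQ or an online one from the preceding 24 hours. With the planning values under Target Recruitment Sample Size (100 participants, 50% flaring), that is 100 × 0.50 = 50 confirmation occasions. The number affected is at most 50. It is lower by those covered by the online exception, and by any confirmed at months 6, 9 or 12 if the assessment there precedes the consultation. The article gives nothing from which to estimate these reductions.

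**Step 6: route to DAS28-CRP.** The patient VAS is one of four components. In the visit sections a single swollen joint is enough for flare without any VAS. Primary Analyses defines the outcome by DAS28-CRP alone, so the VAS can matter there. Whether knowing the verdict and having been treated raises or lowers a patient's rating cannot be settled from the documents.

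**The case against.** A reader might infer that the patient-reported flare label as a whole, and the primary endpoint with it, are contaminated. The documents do not support that.

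- **Most labels are home responses.** Step 4 shows that visit-day forms are a small minority. This stands, although sensitivity depends on the records around confirmed flares, where the share is much larger.
- **The order is inferred and covers only some visits.** It rests on one sentence, used at month 3 and at ad hoc visits. Months 6 to 12 are silent, and no sentence says that patients without a flare are told so first. Delay to Final DAS28-CRP Calculation adds that the final score waits for CRP, so some verdicts do not exist when the form is filled in. The same section says, however, that the partial score usually indicates the final status.
- **Ad hoc attenders already suspect a flare.** Few of them would have answered no, so inflation of sensitivity there is probably small. The likelier effect at those visits is on flares that are not confirmed.
- **No percentage can be defended.** One could assume a true sensitivity and a switching rate and compute an inflated value, but the article supplies neither. Secondary Analyses describes refitting the landmarking model to RA-FQ flare and comparing its predictions with clinical flare. It does not describe tabulating the visit-day answer on its own. Any such figure would be illustrative only.
- **The endpoint effect is limited.** The VAS is one component of four, and Clinical Discretion already expects the study decision to match the clinician's when an elevated score is discounted.
- **This is a condensed article.** The order of forms may be set out in a fuller protocol, and the reference to a schedule 6.3 points to one. That would excuse silence. At month 3 and ad hoc visits, though, the article states a sequence, and that sequence is the one that causes the difficulty.

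These points reduce the scope and remove any claim to a known size. They leave the avoidable dependence in place.

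**Conclusion.** The concern holds in limited form. At month 3 and ad hoc visits, the stated sequence allows the patient VAS, and any visit-day RA-FQ not covered by the 24-hour online exception, to be answered with knowledge of the ROADMAP verdict. For months 6, 9 and 12 the order is open. The consequence is a risk of upward bias in agreement between patient-reported and clinically confirmed flare. Its size is unknown and depends on how often patients change their answer. At most about 8% to 9% of RA-FQs are exposed, but they include those nearest to confirmed flares. The possible effect on DAS28-CRP is secondary and of uncertain direction.

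The conclusion assumes that already treated means the consultation came first, and that the verdict was shared with the patient. It is worth acting on now because a pre-consultation answer cannot be recovered later, nor can affected forms be identified if timing is not recorded. Results reports 16 participants recruited by 1 July 2026 against a target of 100, so the 84 still to be recruited could be protected.

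**What to change.** 1. At the month 3, 6, 9, 12 and ad hoc visits, state that the participant completes the patient VAS, RA-FQ and HAQ-DI on arrival, before the ROADMAP consultation and before the joint examination. The RA-FQ may instead be completed online in the preceding 24 hours, as now.
2. Add a field to each form recording whether it was completed before or after the consultation.
3. State that the accuracy and agreement analyses use RA-FQs completed before the consultation. Where the visit-day form came afterwards, substitute the last RA-FQ completed remotely.
4. Leave baseline as it is.

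The cost is a reordering of forms at visits already attended, one tick-box, one sentence of analysis text and minor coordination in the clinic waiting area. No visit is added and clinical care is unchanged.
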